#### Secondary outcome.

The patient’s vital signs, including: oxygen saturation, heart rate, blood pressure, will be measured at T0 (before inhalation), T2 (two minutes after inhalation), and T3 (five minutes after inhalation). At the end of the procedure, the subjects will be asked what side effects occurred during the intervention and the consumption of adjunctive analgesics will be recorded. Patient and technician satisfaction and willingness to re-use analgesic gas were also secondary outcomes. Vancouver scar assessment scale and ADL scale were used to observe the scar improvement and functional rehabilitation of patients at T5(Four weeks after intervention), respectively. The purpose of this study is to control acute pain during burn rehabilitation, and the effect of scar treatment is indirect, so scar score and functional improvement are set as secondary outcomes.

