### Randomization, allocation, concealment and blinding

Randomization will perform by statistical experts, using SPSS 27.0 software randomly assigned patients 1: 1 to the intervention group versus the control group. The experimental group will be given nitrous oxide inhalation and conventional treatment, while the control group will be given placebo (100% oxygen) inhalation and conventional treatment. Before the trial begins, the project manager will prepare a series of opaque envelopes, each containing a card with treatment assignment written on it (“nitrous oxide group” or “placebo group”). When the patient meet the inclusion criteria and completed the baseline assessment, the project manager will randomly select an envelope from it and determine the allocation of the patient based on the card inside the envelope. Grouping will be confidential to patients and other investigators. The process of extracting the envelope is free from external interference, and the envelope is immediately destroyed to ensure the concealment of the distribution. The devices for both groups of gases are identical in appearance and are both labeled A or B. Neither the investigators nor the subjects involved in the trial could distinguish gases by smell and appearance. A researcher who is not involved in the evaluation will connect the patient to the gas device during the treatment and ensure the proper inhalation of the gas. Assessments will be performed independently by another investigator according to pre-set criteria and time points. During this trial, if the patient has serious side effects and other emergencies, the preset emergency unblinding procedure should be followed, and corresponding treatment measures should be taken to ensure the safety of the patient. Statistical analysts are also unaware of patients’ grouping and treatment measures.

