The intervention group will be given diluted nitrous oxide inhalation on the basis of conventional treatment. Prior to the intervention, a trained nurse will inform the patient of the use and precautions of the inhalation valve. Two minutes before rehabilitation training, patients in the intervention group will inhale premixed 65% N2O through a mask with a self-controlled inhalation valve until the end of rehabilitation training; The control group will be given continuous oxygen inhalation. These two gases are inhaled and stopped by a patient-controlled valve to facilitate observation of the state of consciousness (the patient will release the valve when the optimal medication status is reached).The intervention will be performed once daily for 30 minutes for 4 weeks.The conventional treatment approach includes the following aspects: 1. The patient uses drugs as directed by the doctor during hospitalization. 2. Therapist’s psychological counseling to patients before and during operation. Patients in both the intervention and control groups will have continuous blood oxygen saturation and heart rate monitored, and blood pressure will be measured before, during and after the intervention. If an adverse reaction occurs, the inhalation should be stopped immediately and oxygen should be given. The adverse reaction will disappear within a few minutes.

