### Data management and analysis

In order to ensure the accurate entry of data, two independent personnel enter the data respectively and compare them to ensure consistency. In order to improve quality, researchers are trained before studying. The senior academic statisticians in the group regularly checked the data, including missing values, outliers, etc., and corrected them in time.Missing data from subjects who withdraw from the study will be imputed using multiple imputation methods. Shortly after project initiation, a data monitoring committee (DMC) composition and audit system will be established to monitor data collection and management and patient safety throughout the study. Four professional therapists and nurses, two pain management specialists, and a senior academic statistician who serves as chair of the board will serve as members. Patient safety is monitored and managed by professional therapists and pain management experts.All information will be stored confidentially in the office. Replace all identifying information of the participant, such as name and gender, with a code and always keep it confidential, with only the project manager or attending physician knowing the patient’s personal information. In addition, none of the reports about this study will disclose the personal information of patients.

Statistical analysis will perform using spss.27, with an alpha set at 0.05. The mean (standard deviation), median (interquartile range), minimum value, maximum value and proportion (95% confidence interval) of quantitative data will be listed, and the count data will be described in quantity and percentage. Mean comparison between the two groups will be performed using t-test (normal distribution) and Mann-Whitney test (non-normal distribution). Chi-square test will be used to compare proportions.A value of P < 0.05 will be considered statistically significant.

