Nitrous oxide has shown many advantages in conscious analgesia compared to conventional opioid analgesics. It is an inhaled gas by self-administration and has analgesic, sedative, anxiolytic characteristics. Nitrous oxide has been widely used in recent years, such as dentistry, emergency department, obstetrics and gynecology, pediatrics, postoperative analgesia and other clinical disciplines. It has been reported that a mixture of 20% nitrous oxide and 80% oxygen has an equivalent to 15 mg Comparable analgesic effect of morphine as well as good sedation [23]. It begins to work 30 seconds after inhalation, peaks in two minutes, and the effect disappears within 5 minutes after withdrawal, with mild adverse effects.In addition, it can produce analgesic effects without changing consciousness and cognitive state, which can improve the cooperation of burn patients.

Although nitrous oxide is simple to operate and has mild side effects, it can also be life-threatening in some cases. The replacement of oxygen in the alveoli by nitrous oxide leads to a sudden drop in the partial pressure of blood oxygen, which may lead to hypoxia and asphyxia, which often occurs when the oxygen supply equipment fails and excessive sedation leads to spontaneous respiratory depression. Therefore, it is recommended to use a pre-mixed oxygen/nitrous oxide mixture and monitor with a pulse oximeter. Craniocerebral patients, intestinal obstruction and other patients will have fatal consequences such as cerebral hernia and intestinal perforation. Safety management personnel must strictly grasp the contraindications of nitrous oxide, learn to observe the symptoms of side effects and master first aid measures during training. Diluted nitrous oxide is often stored in cylinders and used through valves to facilitate transportation. Nitrous oxide gas is not expensive, and cylinders and valves can be used repeatedly. Therefore, regular maintenance of equipment and use according to specifications can greatly save costs. Monitoring patients’ vital signs outside surgery is a tricky task. Generally speaking, we can only monitor through portable sphygmomanometers and finger clip oximeters. The disadvantage is that we cannot monitor blood pressure dynamically, but this is enough for the key indicators that need to be monitored.

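### The planned between-arm comparison of oxygen saturation is confounded by inspired oxygen (65% N2O mixture against 100% oxygen), and no per-patient saturation outcome is defined alongside it

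*Protocol article*

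**What the plan says.** All references are to the protocol article.

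- **Gases.** Under Interventions, "patients in the intervention group will inhale premixed 65% N2O through a mask". Under Randomization, allocation, concealment and blinding, "the control group will be given placebo (100% oxygen) inhalation and conventional treatment". The balance of the N2O mixture is not stated. The Discussion supports reading it as oxygen, since "it is recommended to use a pre-mixed oxygen/nitrous oxide mixture".
- **Outcome.** Under Secondary outcome, "oxygen saturation, heart rate, blood pressure, will be measured at T0 (before inhalation), T2 (two minutes after inhalation") and at T3, five minutes after inhalation.
- **Analysis.** Under Data management and analysis, "Mean comparison between the two groups will be performed using t-test (normal distribution) and Mann-Whitney test (non-normal distribution"), with significance at P < 0.05. This is a general rule and does not name SpO2. The section also lists minimum and maximum values for quantitative data and a chi-square test for proportions.
- **Risk.** The Discussion describes hypoxia as a route by which N2O can threaten life: "The replacement of oxygen in the alveoli by nitrous oxide leads to a sudden drop in the partial pressure of blood oxygen".
- **Other capture of hypoxia.** SpO2 is monitored continuously in both arms (Interventions). Oxygen deficiency is on the side-effect list, and therapists record side effects during and after inhalation (Safety).
- **Acknowledged limit of the control.** The Limitation section concedes that pure oxygen may not be inert, but discusses this only for mood and pain, not for SpO2.

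**The concern.** SpO2 is the direct measurement of the risk that the Discussion singles out, and the trial's objective covers safety as well as efficacy. The two arms differ in N2O and also, by at least 65 percentage points, in inspired oxygen. The outcome compared is itself a measure of oxygenation, so the control gas acts directly on it.

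Two misreadings become possible if the stated rule is followed:

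1. A significantly lower SpO2 on N2O may be reported as an adverse effect of the gas when no patient was hypoxic and pure oxygen simply raised the control values.
2. A non-significant difference may be reported as reassurance when a few patients had marked falls that a mean or rank test barely registers.

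The abstract's discussion links wide adoption to the absence of serious side effects, so either misreading would bear on the trial's conclusion.

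**Working it through.** **The plan's own figure.** The document gives no SpO2 mean, SD or event rate, so there is no SpO2 figure to reproduce. Its one power statement concerns pain: 9 per group, effect size 1.68, two-sided alpha 0.05, power 91.67%. The exact noncentral-t calculation gives 0.91667, so it is correct, but it says nothing about SpO2. The input used below is the planned 40 per group (Sample size estimation).

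**Step 1: oxygen content.** 100 − 65 = 35% at most in the N2O arm, against 100% in the control. The difference is at least 65 percentage points.

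**Step 2: can the test be significant without hypoxia?** For a mean gap *g* and common SD *s*, t = g / (s × √(2/40)), with a two-sided 5% critical value of about 1.99 on 78 df. The gaps and SDs are assumptions.

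| Assumed SD | t for a 0.7-point gap | t for a 1.5-point gap |
|---|---|---|
| 1.0 | 0.7/0.224 = 3.13 | 1.5/0.224 = 6.71 |
| 1.5 | 0.7/0.335 = 2.09 | 1.5/0.335 = 4.47 |
| 2.0 | 0.7/0.447 = 1.57 | 1.5/0.447 = 3.35 |

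A gap such as 98.0% against 99.5% is significant across this range of SDs. A 0.7-point gap is significant at SD 1.0 and 1.5 but not at 2.0.

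A simulation allowed unequal SDs and the ceiling at 100%. The N2O mean was 97 or 98 with SD 1.5, taken as unchanged from T0. The control mean was 1 to 2 points higher with SD 0.8. The t-test was significant in 96% to 100% of trials, although by construction N2O had lowered nobody's saturation.

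**Step 3: can the test miss desaturation?**

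- *Mean, one patient.* One patient at 85% and 39 at 98%: (39 × 98 + 85)/40 = 97.68, a shift of about 0.3 points.
- *Mean, two patients.* With 2 of 40 on N2O at 85% and everyone else in both arms around 99%, the expected shift is 2 × (99 − 85)/40 = 0.70 points. The outliers also inflate the arm's SD, and in simulation the t-test was significant in about 5% of trials, no more than its nominal error rate.
- *Ranks, the same two patients.* They take ranks 1 and 2, and the other 78 share ranks 3 to 80 (average 41.5). The expected rank sum on N2O is 3 + 38 × 41.5 = 1580, against 40 × 40.5 = 1620 under no difference. Ignoring ties, the SD is √(40 × 40 × 81/12) = 103.9, so the shift is 40/103.9 = 0.38 SD. The Mann-Whitney branch does not help.

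**Step 4: what a per-patient proportion can deliver at this size.**

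- Chance of at least one event in 40: 1 − 0.95^40 = 87% at a true rate of 5%, and 1 − 0.99^40 = 33% at 1%.
- Upper limit with 0 events in 40: 1 − 0.05^(1/40) = 7.2% (one-sided 95%), or 1 − 0.025^(1/40) = 8.8% (two-sided exact).
- Power of Fisher's exact test against a control rate of 0%: 1%, 21%, 57% and 84% at true rates of 5%, 10%, 15% and 20%.

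A proportion is therefore useful as an estimate with its interval, not as a significance test.

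**The case against.** The strongest case against is that the SpO2 mean comparison is pieced together from a general sentence, and that the protocol already has other routes to hypoxia. Continuous monitoring runs in both arms. Oxygen deficiency is a recorded side effect and can be counted and compared as a proportion. Minimum values are listed, so a reading of 85% at a scheduled time would appear in the table. The T0 value allows change within the N2O arm to be examined. A data monitoring committee oversees safety. Thresholds and change-from-baseline tables commonly sit in an analysis plan, which is not shown.

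Much of this stands. A reader might infer that the trial cannot show whether N2O lowers saturation, or has no means of detecting hypoxia. The documents do not support that. Pure oxygen is a demanding comparator for SpO2, so a value close to control would argue against an average fall; only a lower value is ambiguous. Nor does the difference reflect the control gas alone: both gases contribute.

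What the objection does not remove is the following.

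- The scheduled readings cover the first five minutes of a 30-minute session, and the document does not say that the continuous readings become outcome data.
- The side-effect entry has no SpO2 definition, and patients questioned at the end of the procedure cannot report a saturation.
- The listed minimum is a group descriptive statistic. It is not stated to be each patient's lowest value or a count below a limit.
- The missing threshold alone could be left to an analysis plan. The combination of a stated test, a stated pure-oxygen control and a Limitation section that stops at mood and pain is in the article itself.

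**Conclusion.** The concern holds in a limited form. Following the stated rule gives an SpO2 comparison confounded by inspired oxygen. A lower value on N2O cannot be attributed to N2O as such, and neither a mean nor a rank comparison at T2 and T3 is sensitive to a few desaturating patients. The planned monitoring, side-effect recording and minimum values mean that hypoxia can still be noticed, but none is a defined per-patient SpO2 outcome. No figure in the document is wrong on this point.

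The size is illustrative only. Every SpO2 mean, SD and event rate above is an assumption, and the 35% oxygen content is inferred. The direction does not depend on the exact values, but significance for small gaps does (t = 2.09 at SD 1.5, 1.57 at SD 2.0). The change is worth making, but the matter does not threaten the primary pain analysis.

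**What to change.** 1. Under Secondary outcome and Data management and analysis, make the SpO2 safety summary per patient within each arm: the change from the patient's own T0 value; the patient's lowest value, using the continuous monitoring where it is recorded; and the number and proportion of patients below a limit that the sponsor fixes in advance, with an exact 95% confidence interval.
2. Under Secondary outcome or Limitation, state that a between-arm difference in SpO2 is confounded by inspired oxygen and will not by itself be read as an effect of nitrous oxide.

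The cost is wording and one extra table. No patients or visits are added, and the T0, T2 and T3 readings are already planned; the lowest value over the whole session depends on the continuous readings being stored. Precision remains limited at 40 per arm: no events among 40 is still compatible with a true rate of up to about 7.2% (one-sided 95% limit). The table should therefore be presented as estimation and not as proof of safety.

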**Discussion:**

If the experimental results show that diluted nitrous oxide can bring good analgesic effects without serious side effects, it can improve patients’ compliance with rehabilitation treatment and quality of life, and it is even widely implemented in hospitals and rehabilitation institutions.

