Operative pain triggered by wound debridement, physical therapy, and rehabilitation exercises exacerbate the suffering of burn patients [8]. Poor pain control can lead to severe sequelae, including post-traumatic stress disorder (PTSD), acute stress disorder (ASD), depression, decreased mobility, delayed return to functional status, opioid dependence, and chronic pain syndrome, among others [9]. Good pain control and wound healing are considered very important throughout the burn recovery process. Despite the significant effect of opioids on acute pain, they carry a high risk of developing adverse effects such as delayed wound healing, respiratory depression, opioid-induced hyperalgesia, pruritus, acute urinary retention, opioid tolerance, dependence, addiction, and overdose-related death [10]. In recent years, music, hypnosis and virtual reality have been found to be useful non-drug analgesic measures. But because these are just relaxation and distraction techniques, it is difficult to achieve the same level of analgesia as medications.Many studies have shown that nitrous oxide can provide significant analgesic effects in different procedures, for example, dental surgery sedation and analgesia [11], acute injury sedation and analgesia [12], cancer pain [13], bone marrow biopsy [14], invasive operation in pediatrics [15],and labor analgesia,etc [16]. Patients inhale the gas through the self-controlled valve, and the common side effects are dizziness, nausea, vomiting, etc., which can disappear within five minutes after stopping the drug. Under the premise of strict control of contraindications, no serious complications have been found.

There is currently a lack of trials evaluating the efficacy of nitrous oxide in the treatment of pain during rehabilitation training in burn patients. Therefore, the aim of this study was to evaluate the analgesic effect of N2O in burn patients undergoing rehabilitation training by means of a randomized double-blind controlled trial. We hypothesized that its analgesic properties would reduce pain during rehabilitation training in burn patients with few side effects compared to placebo.We designed this study protocol to test and verify this hypothesis.

Objective: This trial was designed to evaluate the efficacy and safety of diluted nitrous oxide in the treatment of acute pain caused by rehabilitation training in burn patients.

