### Safety

Side effects of nitrous oxide include dizziness, headache, nausea, vomiting, drowsiness, euphoria, lack of oxygen, arterial hypotension, bradycardia, etc. Therapists monitor and record in a timely manner during administration and after discontinuation. When the above adverse reactions occur, stop gas inhalation and give oxygen to the patient, then the discomfort will be relieved within five minutes [18–19].

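### The stated side-effect question covers only the session, so delayed or cumulative effects of 4 weeks of daily gas may be under-ascertained

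*Protocol article*

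**What the plan says.** - **Objective** (Introduction): "This trial was designed to evaluate the efficacy and safety of diluted nitrous oxide", for acute pain caused by rehabilitation training.
- **Exposure** (Interventions): "The intervention will be performed once daily for 30 minutes for 4 weeks".
- **Patient question** (Secondary outcome): "At the end of the procedure, the subjects will be asked what side effects occurred during the intervention". The sentence fixes both the time of asking and the recall window.
- **T5** (Secondary outcome): placed four weeks after intervention and assigned the Vancouver scar scale and the ADL scale. No side-effect item is named.
- **Therapist recording** (Safety): "Therapists monitor and record in a timely manner during administration and after discontinuation". How long the period after stopping lasts is not given. For a patient who reacts, the gas is stopped and oxygen given, and "then the discomfort will be relieved within five minutes".
- **In-session monitoring** (Interventions): "Patients in both the intervention and control groups will have continuous blood oxygen saturation and heart rate monitored", with blood pressure taken before, during and after.
- **Oversight** (Data management and analysis): a data monitoring committee is to be set up "to monitor data collection and management and patient safety throughout the study".
- **Intended use** (Abstract, Discussion): if results show that "diluted nitrous oxide can bring good analgesic effects without serious side effects", the authors foresee wide use in hospitals and rehabilitation institutions.

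**The concern.** The question put to patients looks back over the intervention just given. The article expects side effects to pass within minutes of stopping the gas, and the recall window builds that expectation in. An effect that appears later the same day, or that builds up over repeated sessions, falls outside the window and is recorded only if the patient volunteers it or staff happen to notice it.

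This matters because the exposure is repeated. Most of the uses cited in the Introduction are procedures such as dental surgery, injury care, biopsy and labour, although cancer pain is also listed. The Conclusion presents the trial as the first randomised one in this setting, so how well daily repetition is tolerated is part of what it could show. If delayed effects go unrecorded, absolute side-effect rates are understated. If those effects are due to the gas, the difference between the arms shrinks as well.

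**Working it through.** The article gives no figure for side-effect rates or coverage, so there is none to reproduce on this point. Its one power figure (91.67% with 9 per group at effect size 1.68) reproduces with the exact two-sample t-test, but nothing below depends on it.

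**Step 1. Which period does each stated route cover?**

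| Route | Section | Period covered |
|---|---|---|
| Question to patient | Secondary outcome | Effects during the intervention, asked at its end |
| Therapist recording | Safety | Inhalation and an unspecified time afterwards |
| SpO2, heart rate, blood pressure | Interventions | Tied to the session |
| Data monitoring committee | Data management and analysis | Whole study, but it can review only what is collected |
| T5 | Secondary outcome | Scar and ADL scales named, no side-effect item |

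No row collects symptoms for the interval between sessions or for the course as a whole.

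**Step 2. How much exposure is there?** The schedule is 30 minutes once daily for 4 weeks. The number of sessions per week is an assumption.
- Seven a week: 4 × 7 = 28 sessions; 28 × 30 = 840 minutes = 14 hours per patient.
- Five a week: 4 × 5 = 20 sessions; 20 × 30 = 600 minutes = 10 hours per patient.

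**Step 3. What share of a treatment day is covered?**
- Session only: 30 / 1,440 = 2.1%.
- Session plus the five minutes in which effects are said to resolve: 35 / 1,440 = 2.4%.

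These are shares of clock time. They would equal shares of events only if risk were uniform over the day, which the documents do not suggest.

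**Step 4. Which way does the error go?** Let s be the proportion of patients in an arm with an in-session effect, b the further proportion whose only effect arises between sessions, and c the fraction of the latter that becomes known without being asked for. Then

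- true proportion = s + b;
- recorded proportion = s + c·b, which is too low by (1 − c)·b;
- if c is the same in both arms, the recorded difference between arms is Δs + c·Δb instead of Δs + Δb.

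With c below 1, absolute rates are understated whenever b is above 0. The between-arm difference is attenuated when Δb has the same sign as Δs. The documents give neither b nor c, so the bias cannot be given a number.

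**The case against.** Five points can fairly be made on the other side.

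1. **Other routes exist.** A reader might infer that the end-of-procedure question is the only safety collection. It is not: therapists record during and after inhalation, vital signs are monitored, a committee oversees safety, and an emergency unblinding procedure covers serious side effects. This stands. The word *only* applies to the patient question alone.
2. **The safety objective is addressed.** A reader might also infer that it goes unanswered. That is too strong. The objective concerns acute pain in training, and the acute effects listed under Safety are captured and can be compared between arms. The Abstract's conclusion is conditional and speaks of serious effects, which are more likely than mild ones to surface unasked.
3. **Coverage is not bias.** It is tempting to say that about 98% of the risk goes unobserved. The documents do not support this. They say the effect of the gas is gone within five minutes of withdrawal, and they report no delayed or cumulative effects.
4. **Not everything is visible.** The schedule of assessments (Fig 1) is not shown, and the full protocol behind the article may contain further adverse-event rules. This stands as a reservation. The point nevertheless rests on a rule that the article itself states, with its timing and recall window, and not merely on silence.
5. **The wording is ambiguous.** The procedure could mean each daily session or the whole course. The session reading is the more natural one, because every assessment point before T5 lies within a session. On the course reading, the text would still need to say so.

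**Conclusion.** The point holds in a limited form. As written, the patient question covers the session, and no visible text collects side effects between sessions or over the 4-week course. Delayed or cumulative effects may therefore be under-ascertained, and the safety objective is answered mainly for acute, in-session effects. Any error runs towards fewer recorded side effects. Its size cannot be derived from the documents. What can be stated is the exposure (14 hours per patient at seven sessions a week, 10 hours at five) and the share of each treatment day covered (2.1% to 2.4%).

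This rests on three assumptions: that the procedure means the daily session, that observation after stopping the gas is short, and that neither Fig 1 nor the full protocol adds a side-effect item at T5. It is a cheap improvement to the plan and does not threaten the trial's validity.

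**What to change.** - **At T5**, add to the Secondary outcome section a side-effect question covering the whole 4-week course, put to both arms by an assessor unaware of allocation.
- **Before each session**, where feasible, add a brief question about the time since the last session. This should be written in as a new item: the article describes T0 as a baseline and does not say that it recurs at every session or who records it.
- **In the existing sentence**, state that the end-of-procedure question is asked after each session, if that is what is meant, and give the length of therapist observation after the gas is stopped as currently planned.
- **In reporting**, show in-session and between-session effects separately by arm, with the number of sessions each patient received.
- **If none of this is adopted**, limit the safety conclusion foreseen in the Abstract to the in-session period.

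Cost: the T5 question is 80 short interviews at an assessment already planned. The pre-session question adds up to 27 per patient at 28 sessions, so both together come to 28 × 80 = 2,240 brief entries (20 × 80 = 1,600 at five sessions a week). That is some added daily recording, and more non-specific complaints will be noted in both arms. No extra visits are needed, and sample size and power are unaffected.
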